## Outcome measures

4

### Primary outcome

4.1

The primary outcome in this trial is PR sperm rate (%) at baseline and the 4th, 8th, and 12th week after randomization.

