### Sample size

2.4

Sample size was estimated based on the primary study results. Our previous pre-experiment have shown that the effective rate (*P*_1_) of the YSTL group (treatment group) is 79%, and the effective rate (*P*_2_) of the LOS group (control group) is 54%. The the following formula was used to estimate sample size: 

with a 5% significance level (*α*= 0.05, two-sided) and 90% power (*β*= 0.1), the final sample size has been set at a total of 160 patients (80 in each group), assuming a 15% dropout rate.

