### Statistical analysis

4.5

Statistical Product and Service Solutions (SPSS21.0, International Business Machines Corp., Armonk, NY) software will be performed using for statistical analysis of data by professionals who will be blinded to the whole trial process. Analysis of the efficacy and safety will be based on the principle of intention-to-treat that all random participants will be analyzed. The missing value will be handled by the method of multiple imputations. Data will be presented as mean with standard deviation, median with range, or number with percentage, and different data types will be analyzed by appropriate methods. A repeated-measures multifactorial analysis will be used to analyze value changes of PR sperm rate, PR+NP sperm rate, total effective sperm count, and inner MMP in spermatozoa (See Table 1). The rest of the secondary outcomes will compare the different spouse pregnancy outcomes. Safety outcomes will be compared with the incidence of adverse events in two groups using the *χ*^2^ test. All the statistical tests will be conducted by bilateral difference tests, and if a *P* value is less than 0.05, the data difference will be considered statistically significant.

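### The primary outcome is PR sperm rate at four visits with no deciding visit or model term named, so the stated two-sided 5% error rate is not secured

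*Protocol article*

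**What the plan says.** Section 4.1 (Primary outcome): "The primary outcome in this trial is PR sperm rate (%) at baseline and the 4th, 8th, and 12th week after randomization". The Abstract and the Discussion name PR as the main measure without giving a time point.

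Section 4.5 (Statistical analysis): "A repeated-measures multifactorial analysis will be used to analyze value changes of PR sperm rate, PR+NP sperm rate, total effective sperm count, and inner MMP". One method therefore serves the primary outcome and three secondary outcomes. The section does not name the group effect, the group-by-time interaction or a contrast at a particular visit as the deciding result. The significance rule is general: "All the statistical tests will be conducted by bilateral difference tests, and if a *P* value is less than 0.05" is the threshold for calling a difference significant. No order of testing or adjustment is given.

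Section 2.4 (Sample size) works "with a 5% significance level", "two-sided) and 90% power". Its inputs are effective rates of 79% and 54%, which are proportions of patients. No visit is attached to them.

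**The concern.** A primary outcome needs a measure, a time point and a between-group contrast. Section 4.1 gives the measure and then four time points of equal standing. One of them, baseline, is measured before treatment and cannot show an effect of it.

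A repeated-measures analysis of these data gives at least two between-group results, the group effect and the group-by-time interaction. Comparisons at individual visits are easily added. With one threshold for all tests and no deciding result, a reader of the final report cannot tell whether the result presented as primary was chosen in advance.

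The candidate tests also answer different questions. If baseline is a level of the time factor, the group effect averages over it: a constant post-baseline difference d appears as (0 + d + d + d)/4 = 0.75d. The interaction asks whether the difference changes over time. A week-12 contrast estimates the difference at the end of treatment. The open choice therefore affects the quantity estimated and the power as well as the false-positive rate.

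**Working it through.** **The plan's own figure.** Inputs from section 2.4: rates 0.79 and 0.54, two-sided 5%, 90% power, 15% dropout. With the unpooled formula for two proportions:

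n = [0.79×0.21 + 0.54×0.46] × (1.960 + 1.282)² / (0.79 − 0.54)² = 0.4143 × 10.507 / 0.0625 = 69.65 per arm.

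Multiplied by 1.15 this is 80.1, which agrees with the stated 80 per arm and 160 in total. The trial was thus sized for one two-sided 5% test, on a binary rate. That calculation does not indicate which PR test is primary.

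**Inputs to the error-rate check.** Analysed per arm: 80 × 0.85 = 68. Visits: baseline and weeks 4, 8 and 12 (section 4.1). Threshold: P<0.05 two-sided (section 4.5). The correlation between visits is not given in the article, so I assumed equal correlation between all visits and varied it from 0.3 to 0.9.

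**Closed-form reference points.**
- One test: 5%.
- Group effect or interaction, taken as independent: 1 − 0.95² = 9.75%.
- Any of three independent visit tests: 1 − 0.95³ = 14.3%.

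**Simulation under no effect** (40,000 trials per correlation, Monte Carlo standard error at most 0.2 percentage points):

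| Result allowed to decide | ρ = 0.3 | ρ = 0.5 | ρ = 0.7 | ρ = 0.9 |
|---|---|---|---|---|
| Group effect only | 5.0% | 5.0% | 4.9% | 4.9% |
| Interaction only | 5.1% | 4.8% | 5.1% | 4.9% |
| Week 12 only | 4.9% | 5.1% | 5.2% | 4.9% |
| Group effect or interaction | 9.8% | 9.6% | 9.8% | 9.5% |
| Any of weeks 4, 8, 12 | 13.7% | 12.8% | 11.0% | 8.1% |
| Any of all five | 17.1% | 16.2% | 14.9% | 12.4% |

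The visit rows compare observed PR at each visit. If changes from baseline were compared instead, two changes would have covariance 1 − ρ and variance 2(1 − ρ) each. Their correlation is then 0.5 whatever ρ is, and the any-visit rate is about 13% across the range.

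**Reading.** Any single test named in advance holds 5%. Every rule that leaves two or more routes open exceeds it. If the three post-baseline visits were kept as equal routes, a Bonferroni split would need 0.05/3 = 0.0167 for each.

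**The case against.** The strongest reply is that section 4.5 plans one model covering all visits, and that one term from such a model holds 5%. That is correct. A reader might infer from the four visits and the common threshold that the 5% is already broken, at 14% or 17%. The article does not support this. It plans no visit-by-visit comparisons, and the clause "if a *P* value is less than 0.05, the data difference will be considered statistically significant" is a general threshold, not a rule that any significant PR result makes the trial positive. The two-term figure of about 10% lies closest to the stated method. The figures involving visits rest on tests the article does not mention and on assumed correlations.

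A second reply is that section 4.1 merely gives a measurement schedule. This is largely fair for baseline: section 4.2 uses the same four time points for when semen tests are performed, and an analysis of changes needs a baseline. Nothing suggests that a baseline difference would be claimed as efficacy. The section is still the definition of the primary outcome, and it leaves three post-treatment visits without rank.

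A third reply is that the choice of model term belongs in an analysis plan that is not shown. That holds for the details of the model. The time point, however, is part of the outcome definition; the article does state it, in a form that does not identify one result.

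It is also tempting to call the trial open-label and infer biased assessment. Participants and treating staff are unblinded, but section 2.5 keeps outcome assessors, data managers and statisticians unaware of allocation. That limits biased measurement. It does not settle which result is primary once results are known.

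**Conclusion.** The point holds in this form: the article names no single primary time point or contrast for PR, so the two-sided 5% is not secured. Under no effect, the false-positive rate is about 5% if one test decides, about 10% if either model term may, about 8% to 14% if any post-baseline visit may, and about 12% to 17% if any of these may. These figures assume 68 analysed per arm, equal correlation of 0.3 to 0.9 between visits, normally distributed data and, for the last two ranges, visit tests that the article does not itself plan. The documents do not show that the error rate will in fact exceed 5%; that depends on a choice they leave open.

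A separate matter remains. Section 2.4 sizes the trial on a binary effective rate, so the stated 90% power does not carry over to a contrast in PR at any visit.

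**What to change.** In sections 4.1 and 4.5, state one primary test: the between-group difference in PR sperm rate at week 12, the end of treatment, estimated from the repeated-measures model with baseline PR as a covariate, at two-sided 5%. Make weeks 4 and 8 secondary, and describe baseline as a covariate instead of listing it as an outcome. A single pre-named model term would also hold 5%, but week 12 gives a directly interpretable effect at the end of the planned course.

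Section 2.1 says the trial is already running, so the choice should be documented and dated before unblinding. The cost is wording only: visits, measurements and sample size stay as they are. The one loss is that an effect seen only at week 4 or week 8 would no longer count as primary success.

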### Secondary outcomes

4.2

The secondary outcomes will include:

(1)semen parameters including PR+NP sperm rate (%), and total effective sperm count;(2)the inner MMP in spermatozoa; and(3)spouse pregnancy rate (%).

The semen parameters and sperm MMP test will be performed at the baseline, 4th, 8th and 12th week after randomization. The pregnancy outcome will be evaluated at 4 weeks after treatment.

### Safety outcomes

4.3

Safety outcomes will include electrocardiogram , blood tests (including blood routine test, hepatic function, and renal function), urine routine test, and stool routine test. All the safety outcomes will be evaluated at baseline, 4th, 8th, and 12th week. YSTL is an herbal formula that has been used clinically for many years and has satisfactory safety profiles. A general physical examination will be provided at every visit. If an adverse event occurs, clinical investigators will record it in a case record form in detail (including symptoms, occurrence time, duration, examinations, and outcomes). Serious adverse reactions will be reported to the ethical committee of Henan Province Hospital of TCM and rescue procedures will be initiated immediately.

### Quality control and trial monitoring

4.4

Before the start of the trial, all the researchers will receive special training to guarantee the quality of the study. The training includes how to select and exclude participants, how to complete randomization, how to implement interventions correctly, how to record case report forms in a standard way, how to assess outcomes and manage data. Clinical researchers responsible for diagnosis and treatment will be registered TCM practitioners. To improve the compliance of participants, investigators will provide health education, and fully respect the informed consent right of them. Raw data will be recorded in the case record form, and 2 data managers will input the data into the spreadsheet and recheck the data respectively. To ensure the objectivity of the data, the assessment and statistics will be blinded during the trial. The principle researcher will supervise the whole trial.

### Statistical analysis

4.5

Statistical Product and Service Solutions (SPSS21.0, International Business Machines Corp., Armonk, NY) software will be performed using for statistical analysis of data by professionals who will be blinded to the whole trial process. Analysis of the efficacy and safety will be based on the principle of intention-to-treat that all random participants will be analyzed. The missing value will be handled by the method of multiple imputations. Data will be presented as mean with standard deviation, median with range, or number with percentage, and different data types will be analyzed by appropriate methods. A repeated-measures multifactorial analysis will be used to analyze value changes of PR sperm rate, PR+NP sperm rate, total effective sperm count, and inner MMP in spermatozoa (See Table 1). The rest of the secondary outcomes will compare the different spouse pregnancy outcomes. Safety outcomes will be compared with the incidence of adverse events in two groups using the *χ*^2^ test. All the statistical tests will be conducted by bilateral difference tests, and if a *P* value is less than 0.05, the data difference will be considered statistically significant.

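### Baseline PR is listed among the primary outcome times and the repeated-measures analysis names no baseline adjustment; a baseline-adjusted model on weeks 4, 8 and 12 would use the same data better.

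*Protocol article*

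**What the plan says.** Section 4.1 (Primary outcome) reads: "The primary outcome in this trial is PR sperm rate (%) at baseline and the 4th, 8th, and 12th week after randomization". Baseline is thus written into the outcome beside the three post-randomisation visits. Section 4.2 (Secondary outcomes) gives the same schedule for the other continuous measures: "The semen parameters and sperm MMP test will be performed at the baseline, 4th, 8th and 12th week after randomization".

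Section 4.5 (Statistical analysis) states the method: "A repeated-measures multifactorial analysis will be used to analyze value changes of PR sperm rate". The same sentence covers PR plus non-progressive motility (PR+NP), total effective sperm count and mitochondrial membrane potential (MMP), and it refers to Table 1, which is not shown. The section adds "All the statistical tests will be conducted by bilateral difference tests", with a 0.05 threshold. It names no covariate, and it does not say which model term or which visit decides the primary comparison.

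**The concern.** Before treatment, randomised groups differ only by chance. If baseline is one of the repeated response levels, a test of the group main effect averages that null visit with the visits where treatment can act, so it estimates something smaller than the treatment effect. A group-by-time test avoids this but spreads the signal over three degrees of freedom and works through differences from baseline. If the responses are changes from baseline, the null visit drops out, but the baseline measurement error is subtracted in full instead of being weighted by its correlation with follow-up.

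On each reading, information already collected is used less well than it could be. At stake is the chance of detecting a real PR difference, and whether the headline result is a between-group difference in PR percentage points at a named time.

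**Working it through.** **The plan's own figure.** Section 2.4 (Sample size) uses effective rates of 79% and 54%, "with a 5% significance level", two-sided, and 90% power. With unpooled variance, n = (1.960 + 1.282)² × (0.79×0.21 + 0.54×0.46) / 0.25² = 69.7 per group. Multiplying by 1.15 for dropout gives 80.1, which matches 80 per group and 160 in total. This calculation concerns a binary effective rate, so it says nothing about power for PR as a continuous measure.

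**Inputs for the illustration.** From the protocol: 80 per group less 15% dropout, 80 × 0.85 = 68 per arm; two-sided 0.05; four visits. Assumed, because the documents do not give them: difference 0.5 SD at week 12, equal SD at all visits, and the same correlation ρ between any two visits, with ρ = 0.3, 0.5 and 0.7. Two effect shapes over baseline and weeks 4, 8 and 12 are used: constant (0, 1, 1, 1) and linear (0, 1/3, 2/3, 1).

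**Dilution of the group main effect.** Constant: (0+1+1+1)/4 = 0.75. Linear: (0+1/3+2/3+1)/4 = 0.50. These are exact and need no assumption about SD or ρ.

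**Variances per patient, in SD² units.**
- Mean of four visits: (1+3ρ)/4 = 0.475 / 0.625 / 0.775
- Mean of weeks 4–12 minus baseline: (1+2ρ)/3 + 1 − 2ρ = 0.933 / 0.667 / 0.400
- Mean of weeks 4–12 adjusted for baseline: (1+2ρ)/3 − ρ² = 0.443 / 0.417 / 0.310
- Week 12 adjusted for baseline: 1 − ρ² = 0.91 / 0.75 / 0.51

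The mean change therefore has 2.1 / 1.6 / 1.3 times the variance of the adjusted mean.

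**Power.** For single contrasts, power = Φ(δ/√(2v/68) − 1.96), where δ is the expected contrast and v its variance. Example: linear, ρ = 0.5, group main effect: δ = 0.25, v = 0.625, so Φ(1.844 − 1.96) = 45%. Week-12 ANCOVA: δ = 0.5, v = 0.75, so Φ(3.367 − 1.96) = 92%. The group-by-time test uses a noncentral F on 3 and 402 degrees of freedom, with noncentrality (68/2) × Σ(dᵢ − d̄)²/(1−ρ), where dᵢ is the group difference at visit i.

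| Power (%), ρ = 0.3 / 0.5 / 0.7 | Linear growth | Constant effect |
|---|---|---|
| Group main effect, four visits | 56.2 / 45.4 / 38.1 | 88.7 / 79.0 / 70.0 |
| Group-by-time, 3 df | 56.7 / 73.0 / 92.7 | 71.2 / 86.0 / 98.1 |
| Mean change from baseline | 52.1 / 66.3 / 86.7 | 85.5 / 94.6 / 99.6 |
| Week-12 ANCOVA | 86.4 / 92.0 / 98.3 | 86.4 / 92.0 / 98.3 |
| Baseline-adjusted mean, weeks 4–12 | 83.1 / 85.3 / 93.7 | 99.2 / 99.5 / 99.9 |

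Under linear growth, week-12 ANCOVA beats every candidate reading of the plan. Under a constant effect it does not: the group main effect is ahead at ρ = 0.3 (88.7 against 86.4), group-by-time is level at ρ = 0.7, and mean change is ahead at 0.5 and 0.7. The baseline-adjusted mean of weeks 4–12 exceeds all three plan readings in all six cases, though at ρ = 0.7 the margin over the best of them is small.

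**The case against.** The strongest reply is that section 4.5 never says baseline is a response level. That is inferred by reading it with section 4.1, whose list of times could be a measurement schedule, as in section 4.2. The phrase about value changes may mean change from baseline, and covariates and contrasts are often left to an analysis plan. The point about inference stands: a reader might conclude that the protocol commits to baseline as a response, and it does not say so. But section 4.1 does fix baseline as a time of the primary outcome, section 4.5 does fix a method, and the change-from-baseline reading remains less efficient than adjustment. This is therefore an improvement to what is written, not a complaint about missing detail.

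Three further objections also stand. Dilution applies only to the group main effect. Group-by-time is a within-patient comparison and does remove stable differences between men, which is why its power rises with ρ. A repeated-measures model can also yield visit-specific PR differences, so the plan does not preclude a usable effect size; it simply does not name one. Finally, baseline as a response is not inefficient in itself: a longitudinal model with the baseline means constrained equal recovers about the efficiency of ANCOVA. Section 4.5 does not describe such a model.

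**Conclusion.** The point holds as an efficiency improvement that should be made. If the group main effect over four visits is the test, the effect is diluted to 75% (constant) or 50% (linear) of the week-12 difference. If group-by-time or change from baseline is the test, there is no dilution, but power is still lost relative to a suitable baseline-adjusted contrast. The loss ranges from large (linear, ρ = 0.3: 52–57% against 86%) to negligible (constant, ρ = 0.7: 98.1% or 99.6% against 99.9%).

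The power figures rest on an assumed 0.5 SD difference, equal SDs, equal correlations and two effect shapes. Two stronger inferences are not supported. One is that the trial is underpowered for PR, or gives up power it is known to have: the documents give no PR difference, SD or correlation, and the sample size rests on a binary rate. The other is that a week-12 ANCOVA is always best: with a constant effect it is not.

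**What to change.** In section 4.1, define the primary outcome at post-baseline times only, and describe baseline PR as a covariate.

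In section 4.5, analyse PR, PR+NP, sperm count and MMP with a mixed model for repeated measures on weeks 4, 8 and 12, with treatment, visit, treatment-by-visit and the baseline value of the same measure as covariate. A longitudinal model with baseline means constrained equal is an acceptable equivalent.

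Name one contrast as primary before unblinding: either the week-12 difference, which does better if the effect builds up over treatment, or the mean of weeks 4–12, which does better if it appears early and persists. Report the adjusted between-group PR difference in percentage points with its 95% CI.

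The cost is wording only. Baseline values are already collected for all four measures, and no visit, patient or assay is added.

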### Randomization and Blinding

2.5

Eligible participants who provide informed consent will be randomized at a 1:1 ratio into either YSTL group receiving a 12-week YSTL therapy or LOS group receiving the Levocarnitine Oral Solution therapy. Randomization will be performed based on a random list of numbers generated by SPSS21.0 software (International Business Machines Corp., Armonk, NY). An independent researcher will prepare the assignments in opaque envelopes containing an allocation sequence number and be responsible for the concealment of allocation sequence. Due to the specific nature of the intervention, it is not possible to blind the participants and personnel involved in conducting the trial. Outcome assessors, data managers, and statisticians will be unaware of the treatment allocations.

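### The safety outcomes are serial laboratory and ECG tests, but the only between-group safety comparison named is adverse-event incidence, with no stated link from an abnormal test to an event

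*Protocol article*

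**What the plan says.** Protocol article, section 4.3 (Safety outcomes), lists what is measured: "Safety outcomes will include electrocardiogram , blood tests (including blood routine test, hepatic function, and renal function), urine routine test, and stool routine test". The schedule follows: "All the safety outcomes will be evaluated at baseline, 4th, 8th, and 12th week". The Abstract and the Discussion give the same list, and adverse events are not on it. Section 4.3 handles them separately: "If an adverse event occurs, clinical investigators will record it in a case record form in detail".

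Section 4.5 (Statistical analysis) then gives the safety analysis: "Safety outcomes will be compared with the incidence of adverse events in two groups using the" χ² test. The repeated-measures analysis in that section names four efficacy variables and no safety variable. A general sentence in the same section adds that "different data types will be analyzed by appropriate methods".

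On blinding, section 2.5 says that "it is not possible to blind the participants and personnel involved in conducting the trial", and also that "Outcome assessors, data managers, and statisticians will be unaware of the treatment allocations". Section 4.4 adds that assessment and statistics are blinded during the trial.

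**The concern.** The outcome that is defined and the quantity that is compared are different variables. One is a set of test results obtained on every man at four fixed visits. The other is a count of events that exists only where somebody has made an entry. Moving from one to the other needs a rule for when a result is an event and a person to apply it. The article gives neither.

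The gap matters more in an open-label trial. If the people who decide what to enter know the arm, recording can differ between arms even when the test results do not. Even with perfectly even recording, a modest shift in a liver or kidney value that stays below the level at which anyone enters an event does not contribute to an event count. Safety stands beside efficacy in the aim stated in the Introduction and in section 2.1, so the analysis should use the safety data that the trial collects.

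**Working it through.** The article contains no safety rate, standard deviation or safety power statement, so there is no figure of its own to reproduce on this point. The main check is a comparison of the sections.

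1. *What is measured.* Section 4.3: six kinds of test (ECG, routine blood, liver, kidney, urine, stool), four visits, all participants.
2. *What is compared.* Section 4.5: adverse-event incidence, two groups, χ².
3. *Other named analyses that could take up the tests.* The repeated-measures analysis does not; its list holds only PR rate, PR+NP rate, total effective sperm count and sperm MMP. The safety tests have the same four-visit schedule but are not on it.
4. *The step from test to event.* Section 4.3 says who records an event. No section says what makes a test result an event, or who decides.
5. *Blinding of that step.* Section 2.5 places trial personnel among the unblinded and outcome assessors among the blinded. Neither section 2.5 nor section 4.4 says which of them makes this judgement.

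Two illustrations show what could follow. All rates, shifts and thresholds in them are assumptions.

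*Uneven recording.* Recorded count = true count × proportion recorded.
- True counts equal, 8 of 80 in each arm, recorded at 75% and 40%: 8 × 0.75 = 6 and 8 × 0.40 = 3.2. A difference appears where none exists.
- True counts 10 and 5, recorded at 40% and 80%: 10 × 0.40 = 4 and 5 × 0.80 = 4. A real difference disappears.
- Range: with 8 true cases per arm and recording anywhere from 40% to 80%, the false difference runs from 0 (equal recording) to 8 × (0.80 − 0.40) = 3.2 cases.

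*Loss of information with even recording.* Inputs from section 2.4: 80 per arm, or 80 × 0.85 = 68 after the 15% dropout. Assumed: one laboratory value, normally distributed, shifted by 0.5 SD in one arm; two-sided α = 0.05.
- Comparing means: power ≈ Φ(0.5 × √(n/2) − 1.96). For n = 80, Φ(3.162 − 1.96) = 0.885. For n = 68, Φ(2.915 − 1.96) = 0.83.
- Comparing event incidence, with an event only when the value passes a threshold of t SD: the event probabilities are 1 − Φ(t) and 1 − Φ(t − 0.5). Power is from the normal approximation to the two-proportion test.

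| Threshold t | Event probabilities | Power, 68 per arm | Power, 80 per arm |
|---|---|---|---|
| 2 | 0.0228 v 0.0668 | 0.235 | 0.269 |
| 2.5 | 0.0062 v 0.0228 | 0.124 | 0.139 |
| 3 | 0.0013 v 0.0062 | 0.067 | 0.072 |

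At t = 2 and 80 per arm the expected counts are 80 × 0.0228 = 1.8 and 80 × 0.0668 = 5.3. At higher thresholds they are smaller still and the approximation is rough. The calculation ignores baseline values and repeated visits. It shows the direction and rough scale of the loss, not a forecast for this trial.

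**The case against.** The strongest case on the other side has four parts.

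*The general sentence may cover the tests.* Section 4.5 promises suitable methods for each data type and summaries as means, medians or counts, and it applies intention-to-treat to safety as well as efficacy. A reader might infer from the safety sentence that the test values will not be compared at all. The article does not support that, because nothing excludes them. What stands is that the general sentence names no safety test, while the one sentence written about safety outcomes points to a different variable.

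*Assessment is said to be blinded.* A reader might also infer that an unblinded clinician decides which abnormal results count. The article does not say so. Clinical investigators enter the events, but the judgement on a test result could belong to the blinded assessors. The adjudicator is unspecified, and the blinding is not said to reach this step.

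*The wording is loose.* The sentence could mean that safety outcomes are compared along with event incidence, or that abnormal results are counted as events. On either reading a χ² test needs each result classified as normal or abnormal, and no classification or classifier is given.

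*This belongs in a full protocol or SAP.* Shift tables and abnormality rules often do, and their absence from an article would not be a finding. Here, however, the article is not silent. It fixes a method, and an SAP that followed it to the letter would test adverse-event incidence.

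It is also fair to say that the numerical illustrations are constructed. They show what can happen, not what this trial will produce.

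**Conclusion.** The point holds as a mismatch within the article. Section 4.3 defines serial laboratory and ECG tests as the safety outcomes; the only between-group safety comparison that section 4.5 names is adverse-event incidence. With no rule and no named judge linking the two, a shift not recorded as an adverse event may be missing from that comparison.

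The size cannot be derived from the article. Under the assumed recording rates of 40% to 80%, the false difference with 8 true cases per arm is 0 to 3.2 cases. Under an assumed 0.5 SD shift, power falls from 0.83–0.885 for a comparison of means to about 0.07–0.27 for event incidence. The efficacy analyses are untouched, and the raw safety data are collected in any case. This is an inexpensive improvement to the plan, not a flaw that threatens the primary result.

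**What to change.** Add to section 4.5 that each laboratory and ECG outcome is also summarised and compared by arm:

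- the number of men who move from within the laboratory's reference range at baseline to outside it at any post-baseline visit, or from normal to abnormal for ECG;
- the change from baseline in liver and kidney values;
- classification made without knowledge of arm;
- results given descriptively, with confidence intervals;
- investigator-recorded adverse events in a separate table, with the χ² comparison kept for them.

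The two summaries do different work. The count of moves out of range no longer depends on whether somebody entered an event, but it still reduces each value to yes or no. The change from baseline keeps the information that the threshold calculation shows being lost.

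The cost is some wording and a few more tables from data already collected at four visits. The downside is more comparisons, and so more chance differences, which is why descriptive reporting is preferable to a further set of tests. Nothing in treatment or patient management changes.
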